#### Recruitment {15}

To facilitate recruitment in this trial, without interfering with the standard workflow of the military treatment facility providers and staff and patient care, each site will be supported by a research coordinator who will be responsible for consenting eligible participants and facilitating communication and processes between clinics and the digital CBTI hubs. We remain cautiously optimistic as the volume of patients diagnosed with insomnia annually at each of our participating sites represents more than 10 times our enrollment target.

### Assignment of interventions: allocation

#### Sequence generation {16a}

Eligible participants who provide informed consent will be stratified by the presence or absence of any current sleep, medical, or psychiatric comorbidities (yes/no) and the use of psychotropic medications (yes/no). Within each stratum, participants will be randomized in a 1:1 manner to ICAU or digital CBTI hub at the site level. Randomization within each stratum will follow a permuted block design (block size of three) to ensure that the treatments and clinicians are equally distributed across strata. The use of stratified randomization with permuted block randomization will provide a balance of treatment arms across psychiatric comorbidity and medication use. We considered stratifying on additional covariates (e.g., sex, age, enlisted vs. officer), but this would result in an unreasonably large number of strata, and there is little evidence that these may confound the outcome measures of interest. All analyses, however, will first consider plausible covariates. A computer-generated randomization scheme has been generated for each site.

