
## Methods: participants, interventions, and outcomes

### Study setting {9}

The study will be conducted with service members across three military treatment facilities in the USA. The three military treatment facilities have a dedicated sleep clinic with at least one behavioral sleep medicine provider (physician and/or psychologist) and existing procedures and personnel for insomnia treatment.

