Service members will be excluded from participation if they present with an untreated or under-treated comorbid sleep disorder that requires independent treatment or that may be exacerbated by CBTI interventions (e.g., obstructive sleep apnea, rapid eye movement (REM) sleep behavior disorder, or sleepwalking with a history of injury to self or others). Individuals will also be excluded if they are determined to be in acute psychiatric distress associated with marked impairments in functioning or that limits engagement in CBTI, adversely impacts the risk/benefit ratio of participating in the study, or requires immediate attention (e.g., attempted suicide in the past 6 months, seeking and/or receiving psychiatric treatment that requires inpatient or partial hospitalization level of care, requiring support of an assigned case manager for activities of daily living, active substance use disorder, past or current diagnosis or sub-threshold symptoms of psychotic or bipolar disorders, and untreated seizure disorder). Breastfeeding women or parents of an infant under the age of 3 months will also not be eligible, as their insomnia is confounded by these conditions, and CBTI may create greater-than-expected levels of transient sleepiness or fatigue. These minimal exclusion criteria are designed to support the recruitment of participants who are representative of adults with chronic insomnia and generalizable to real-life findings for military and civilian populations. The exclusion criteria that have been established are intended to minimize the risks associated with study participation. Nonetheless, each referring sleep medicine provider will use their clinical judgment to make determinations about the appropriateness of study participation, including CBTI for the patient, and will determine whether a patient is eligible for the study.

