#### Sample size {14}

Power calculations and sample size were based on a conservative estimate of the non-inferiority margin (NIM) based on our preliminary data and prior studies [53–55] and effect sizes reported in the literature on the effects of CBTI on insomnia severity [56–60], as well as estimates of recruitment feasibility based on patient volume at the participating sites. Specifically, effect sizes in the moderate to very large range (0.50 to 2.15) have been reported for insomnia, depression, and anxiety in military and civilian samples. Thus, we conservatively estimated a NIM of *d* = 0.5 for each outcome of interest for this trial. The NIM of |*d*|= 0.5 set to determine non-inferiority is stringent as it represents 50% of the effect size reported in recent meta-analyses [61–63]. For non-inferiority tests, we set an allowable one-sided type I error rate of *α* = 0.025. Conservatively adjusting for our two a priori *t*-tests (post-treatment and a 3-month follow-up), we use *α** = 0.0125 to determine power. Based on the current patient volume and clinical workflows at the three participating sites, we estimated that a total of 188 patients could be enrolled in this clinical trial over the period of performance. Power calculations using PASS version 23.0.2. [64] yielded 88% power with a full sample of 94 participants per group (our primary strategy and 80% power with a final sample of 140 completers assuming an attrition rate of 25% (*N* = 70 completers per group).

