#### Implementation {16c}

Following participant consent to participate in the study, the coordinator will access the computer-generated randomization file to discover which treatment arm the participant has been randomized to. The participant and the referring sleep medicine provider will be informed of the randomization outcome. For participants randomized to ICAU, the coordinator will facilitate the scheduling of an appointment at the sleep clinic for ICAU through the referring site’s standard operating procedures. For participants randomized to the digital CBTI hub, the coordinator will facilitate a warm hand-off to the clinician affiliated with the digital CBTI hub, and the participant will then initiate CBTI under their close supervision.

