### Assignment of interventions: blinding

#### Who will be blinded {17a}

Given the nature of the study design, blinding of participants or clinicians will not be possible. However, masked data will be provided to the biostatistician who will perform the analyses. Randomization will be unmasked only after analyses are finalized. Furthermore, clinicians providing ICAU or treatment via digital CBTI hubs will not participate in periodic interim analyses of the primary and secondary outcomes to avoid biases and/or changes in practice over the course of the study.

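### A single published block size of three in an open trial makes some allocations foreseeable to the staff who enrol; use undisclosed, randomly varying even blocks

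*Protocol article*

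**What the plan says.** All points are in the protocol article.

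- **Sequence generation {16a}:** "Randomization within each stratum will follow a permuted block design (block size of three"), and "participants will be randomized in a 1:1 manner to ICAU or digital CBTI hub at the site level". The strata are the "presence or absence of any current sleep, medical, or psychiatric comorbidities (yes/no) and the use of psychotropic medications (yes/no"). A computer scheme has already been generated for each site.
- **Who will be blinded {17a}:** "blinding of participants or clinicians will not be possible".
- **Concealment mechanism {16b} and Implementation {16c}:** the site coordinator alone can open the scheme, does so at allocation, and so learns every assignment at the site. Then: "The participant and the referring sleep medicine provider will be informed of the randomization outcome".
- **Who acts before allocation:** the coordinator runs the screening interview and takes consent (Who will take informed consent {26a}; Recruitment {15}). On the provider's side, Eligibility criteria {10} says that "each referring sleep medicine provider will use their clinical judgment to make determinations about the appropriateness of study participation".

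These sections describe no variation in block size, no withholding of the size and no central allocation.

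**The concern.** In an open trial, concealment has two parts: nobody who enrols should be able to read the list ahead, and nobody should be able to work out the next entry from the previous ones. The second fails in part when the block is short, constant and known. It fails even if the list is locked row by row, because the prediction uses only past allocations.

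The people who learn past allocations also influence who enters and when. The document itself supplies a possible motive: its Discussion reserves in-person care for severe insomnia with complex comorbidity, and its Background sees the hub as freeing clinic time for more complex patients. Someone holding that view could wait to enrol a complex patient until in-person care was the likely next arm. The hub would then receive an easier case mix, which pushes the comparison toward non-inferiority, the claim under test. Yes/no strata and ANCOVA on baseline ISI and other measured covariates remove only what they capture.

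**Working it through.** **Inputs.** Two arms, 1:1, block of three, 2 x 2 = 4 strata (Sequence generation); "service members across three military treatment facilities in the USA" (Study setting); "a total of 188 patients could be enrolled in this clinical trial" (Sample size).

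**Length of the lists.** 3 sites x 4 strata = 12 lists; 188 / 12 = 15.7 patients per list; 15.7 / 3 = about 5 blocks. A coordinator can follow lists of that length.

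**Make-up of a block.** Three is not a multiple of two, so no block can be 1:1 and the make-up has to be assumed. In each case below, the observer knows the scheme, the position in the block and the earlier allocations in it. For each position, I take the chance that the next arm is certain and the chance that the best guess is right, and then average over positions.

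*Random make-up.* Each block is 2:1 or 1:2 with equal chance, so AAB, ABA, BAA, ABB, BAB and BBA each have probability 1/6.

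- Position 1: certain 0, correct 1/2.
- Position 2: certain 0, correct 2/3 (after A, two of the three remaining sequences continue with B).
- Position 3: certain after AA or BB, which is 2/6 = 1/3; otherwise a coin toss. Correct = 1/3 + 2/3 x 1/2 = 2/3.
- Average: certain (0 + 0 + 1/3) / 3 = 1/9 = 11.1%; correct (1/2 + 2/3 + 2/3) / 3 = 11/18 = 61.1%.

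*Known make-up* (for example strict alternation of 2:1 and 1:2). For AAB:

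- Position 1: certain 0, correct 2/3.
- Position 2: certain 1/3, correct 2/3.
- Position 3: certain 1, correct 1.
- Average: certain 4/9 = 44.4%; correct 7/9 = 77.8%.

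*Paired* (a 2:1 and a 1:2 block in random order). The first block behaves as random and the second as known: certain (1/9 + 4/9) / 2 = 5/18 = 27.8%; correct (11/18 + 14/18) / 2 = 25/36 = 69.4%.

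**Alternatives.** Fixed even blocks use the same enumeration. For the 4/6 mix, the simulated observer knows that the sizes are 4 and 6 but not their order.

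| Scheme | Certain | Best guess correct | Certain, of 188 |
|---|---|---|---|
| Three, random make-up | 11.1% | 61.1% | 21 |
| Three, paired | 27.8% | 69.4% | 52 |
| Three, make-up known | 44.4% | 77.8% | 84 |
| Fixed 2 | 50% | 75% | 94 |
| Fixed 4 | 33.3% | 70.8% | 63 |
| Fixed 6 | 25% | 68.3% | 47 |
| 4 and 6 mixed, long list | about 5.5% | about 69.3% | 10 |
| 4 and 6 mixed, list of 16 | about 6.0% | about 68.4% | 11 |

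The last column is 188 times the share and ignores unfinished blocks. Unpredictable allocation would give 0% and 50%.

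**Balance.** Blocks of up to 6 allow an imbalance of at most 3 within a list. Paired blocks of three allow at most 2. Blocks of three with random make-up have no fixed bound: each completed block adds or removes one, so five blocks can leave a difference of 5.

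**The case against.** **The largest figure needs an undescribed scheme.** A reader might infer that 44% of assignments are certain. Identical 2:1 blocks would give that, but they would produce a 2:1 trial, against the stated 1:1 and 94 per group. Strict alternation would also give it, but the document describes no such scheme. If three meant three per arm, the block would be six (25%, 68%). This stands: the readings compatible with 1:1 run from 11% (61%) to 28% (69%).

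**The provider sees little.** A reader might infer that any referring provider can predict the next arm. The text says only that the provider is told the result for the participant referred, and contact, screening and consent run through the coordinator. To predict, a provider would need the ordered history of one of 12 lists. This stands for providers. The coordinator does see the whole history.

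**The coordinator can open the list anyway.** True, so block size adds little for that person while the list is in the coordinator's hands. But securing the list would not stop the coordinator from predicting out of past allocations.

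**The bias is unquantified.** A reader might attach a shift in SD units and an inflated error rate. With residual biases of 0.05, 0.10 and 0.15 SD, a hub exactly at the 0.5 margin would pass about 5%, 10% and 17% of the time instead of 2.5% (94 per arm, one-sided 0.025). Those biases are assumptions. If every enrolment were steered with 61% correct guesses, the arms would differ by (2 x 0.611 - 1) = 0.222 times the difference between the steered groups. Biases of 0.05, 0.10 and 0.15 would then need residual differences of 0.23, 0.45 and 0.68 SD after covariate adjustment. Nothing in the document shows that steering would occur or how large it would be.

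**The remedy does not beat three on every measure.** Correct: mixed 4 and 6 leaves guessing at 68 to 69%, above the 61% of random make-up and about equal to fixed six. What it removes is most of the certain foreknowledge.

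**Conclusion.** The point holds at moderate weight. One short, constant, published block size in an open trial gives enrolling staff certain knowledge of about 11% of coming assignments under random make-up and about 28% under pairing, roughly 21 to 52 of 188. This assumes that the observer knows the position in the block and has followed the list; the coordinator can do so, and a referring provider can do so only in part. The possible bias could favour the hub, but the document gives no basis for its size. The sentence needs revision in any case because three cannot give 1:1 within a block, and a careless correction to a fixed two would make half of all assignments certain.

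**What to change.** In Sequence generation {16a}, replace the block of three with even blocks whose size varies at random (for example 4 and 6) within the existing site-by-stratum lists. Keep the sizes in use out of site-facing and public documents until enrolment closes, and regenerate the unused part of each site's scheme. Do not move to a single fixed size.

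Treat this as a complement to keeping the list from the staff who enrol, for instance by central release of each assignment after enrolment is irrevocable. Varying the block size alone does not achieve that.

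The cost is one re-run of the existing computer scheme, one changed sentence, and an imbalance of up to 3 within a stratum list at any time. Allocations already made stay as they are, so the gain applies only to patients not yet randomized.

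### A permuted block of three cannot be balanced for two arms at 1:1, so the stated block size does not ensure the within-stratum balance or the 94/94 split the plan relies on

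*Protocol article*

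**What the plan says.** All of the following is in the protocol article, Sequence generation {16a}, unless noted.

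- Ratio: "Within each stratum, participants will be randomized in a 1:1 manner to ICAU or digital CBTI hub at the site level".
- Block size: "Randomization within each stratum will follow a permuted block design (block size of three").
- Purpose of the blocks: "to ensure that the treatments and clinicians are equally distributed across strata".
- Result claimed: "The use of stratified randomization with permuted block randomization will provide a balance of treatment arms across psychiatric comorbidity and medication use".
- Stratification factors: "stratified by the presence or absence of any current sleep, medical, or psychiatric comorbidities (yes/no) and the use of psychotropic medications (yes/no").
- Status of the lists: "A computer-generated randomization scheme has been generated for each site".

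Study setting {9} gives three facilities. Two binary factors at three sites make 2 × 2 × 3 = 12 site-by-stratum cells. Sample size {14} expects 188 patients and bases its power on equal arms, 94 per group or 70 completers per group. The article mentions no mixture or pairing of 2:1 and 1:2 blocks, no varying block sizes and no third allocation category.

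**The concern.** Blocking guarantees balance only if each completed block, or each short run of blocks, returns to the target ratio. With two arms at 1:1, a block of three cannot do this. The ratio, the block size and the promise of balance, all in one paragraph, therefore do not fit together, and a reader cannot tell which allocation mechanism is in force.

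Three things are at stake: the equal split behind the power statement, the within-stratum balance that justifies stratifying, and, for some list types, how easily the next assignment can be worked out. The last matters because the trial is open-label and the site coordinator who consents participants also has access to the scheme (Concealment mechanism {16b}, Implementation {16c}). The lists already exist, so any error may already be in them.

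A smaller mismatch sits in the same paragraph. Balance is claimed on psychiatric comorbidity, but the factor pools any sleep, medical or psychiatric comorbidity. Balance on the pooled factor does not ensure balance on its psychiatric component.

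**Working it through.** **Inputs.** From Sample size {14}: 188 patients, 94 per group; 70 completers per group after 25% attrition; margin d = 0.5; one-sided α = 0.0125 for power. A true difference of 0 is assumed. From Sequence generation {16a}: two arms, 1:1, block of three.

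**Block arithmetic.** 3 × 1/2 = 1.5 patients per arm, which is not an integer. A block containing both arms is 2:1 or 1:2.

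**The plan's own figure.** The noncentrality is 0.5 × √(n₁n₂/(n₁+n₂)), with n₁+n₂−2 degrees of freedom. At 94/94 it is 0.5 × √47 = 3.428 and the critical t is 2.260, so power is 87.8%. The stated 88% is reproduced.

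**Case A: every block has the same 2:1 composition.**
- Split: 188 × 2/3 ≈ 125 v 63.
- Noncentrality: 0.5 × √(125 × 63/188) = 3.236. Power is 83.5%, a loss of about 4 points.
- With 25% attrition: 188 × 0.75 = 141, so 94 v 47. Noncentrality is 0.5 × √(94 × 47/141) = 2.799 and power is 70.3%.
- The fair comparator is 70/70 by the same method: noncentrality 2.958, power 75.5%. The allocation accounts for about 5 points. The article's 80% at 70 per group does not reproduce at α = 0.0125; that is a separate matter and should not be charged to the block size.
- Assignments fixed by earlier ones: the third always is, and the second is when the single-place arm comes first (probability 1/3). The share is (1 + 1/3)/3 = 4/9 = 44%.

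**Case B: 2:1 and 1:2 blocks mixed at random with equal probability.**
- About 188/3 ≈ 62 blocks, each adding +1 or −1 to the arm difference. SD = √62 = 7.9, and the binomial probability of a difference of 12 or more is 0.16.
- Power at 100/88, a difference of 12: noncentrality 3.421, power 87.6%, against 87.8% at 94/94.
- Assignments fixed by earlier ones: only the third, and only when the first two agree (probability 1/3). The share is (1/3)/3 = 11%.

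The table gives 2,000 simulated trials per scheme, with 188 patients over 12 equally likely cells. Equal cells are an assumption, because the article gives no stratum prevalences.

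| Scheme | SD of overall difference | 95th percentile, overall | 95th percentile, largest within-cell difference |
|---|---|---|---|
| Block of 3, random mix | 8.2 | 16 | 7 |
| Block of 4 | 3.2 | 6 | 2 |
| Block of 6 | 3.8 | 8 | 3 |
| Simple randomisation | 13.6 | 26 | 11 |

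**Case C: each 2:1 block paired with a 1:2 block.** Enumerating all orderings shows exact 1:1 every six patients and a running difference that never exceeds 2 within a stratum.

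**The case against.** The strongest reply is that an odd block size does not by itself rule out a 1:1 list. Case C uses blocks of three, is exactly 1:1 every six patients, and holds within-stratum imbalance to 2, the same bound as a block of four. The word three may also misreport what was generated; three per arm, meaning a block of six, is one possible slip, though that is conjecture. The lists have not been seen.

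This stands, and it limits the point. A reader might infer that the 94/94 split will not occur, or that the trial is really randomising 2:1. The article supports neither. A fixed 2:1 list contradicts its own 1:1 ratio and its equal group sizes, so the power losses in Case A are a worst case. The 44% also belongs to Case A alone. Under random mixing the share is 11%, lower than the 33% for a known block of four, so predictability is not a general argument against blocks of three.

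The reply does not rescue the text. The article describes neither pairing nor any other device that would restore 1:1, so what it specifies does not deliver what it promises. Nor is this a detail left to a fuller document: the block size is stated, and it conflicts with the ratio stated in the preceding sentence.

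**Conclusion.** The point holds as an internal inconsistency. With two arms at 1:1, the stated block size does not ensure equal distribution within strata or the 94/94 split used for power.

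- **Worst case (one 2:1 composition):** about 125 v 63; power 83.5% instead of 87.8%; after 25% attrition 70% against 75.5% at 70/70; 44% of assignments fixed by earlier ones.
- **Random mixture:** power essentially unchanged, but imbalance is unbounded (SD about 8 overall, 16% chance of a difference of 12 or more) and the guarantee of within-stratum balance is lost.
- **Paired blocks:** no material harm, but the text would still need to say so.

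The power figures assume a true difference of 0 and the article's margin and α. The simulated figures also assume equal cell sizes. Which case applies is unknown, so it does not follow that every list must be replaced. The text must be corrected in any case. The psychiatric comorbidity wording is a minor looseness that rewording resolves; it is no reason to change the stratification.

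**What to change.** 1. Check the lists already generated for each site and state their actual block sizes and composition in Sequence generation {16a}. If the blocks are even, correcting the sentence is enough. If they are odd but paired to restore 1:1, describe the pairing.
2. If the blocks are odd and not paired, regenerate the unused part of each list within stratum, using even block sizes that vary at random (for example 4 and 6). Conceal the sizes from those enrolling. Since the site coordinator now has access to the scheme, concealment requires that this person cannot view assignments ahead of time.
3. Keep all past assignments, document the change and its date, and report the achieved split.
4. Reword the balance claim to the factor actually stratified on: any sleep, medical or psychiatric comorbidity.

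The cost is a list check, possibly a new computer-generated list, and a short amendment.

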#### Concealment mechanism {16b}

Access to the computer-generated randomization scheme will be limited to the site coordinator and only be accessed at the time of allocation to the treatment arm.

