### Who will take informed consent? {26a}

After being informed of the study by their sleep medicine provider, service members who express interest in participating in the study will be informed of how to contact the site research coordinator directly or may agree to be contacted by the site research coordinator. At their first contact with the coordinator, the coordinator will review details about the study aims, procedures, and risks following a script to verify the consistency and completeness of the information provided. They will also answer any questions the potential participant may have about the study. If the person declines participation, the coordinator will contact the referring sleep medicine provider to let them know that the patient should be scheduled for follow-up care at the local sleep clinic. For participants who remain interested in participating in the study, after receiving information about the study and obtaining answers to questions that may have arisen, oral consent will be obtained to conduct a brief screening interview to confirm eligibility. Upon verification of eligibility, participants who express the desire to participate in the study will then review the consent form with the coordinator.

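### The coordinator who takes consent also holds the pre-generated site list, so concealment from the recruiter is not ensured

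*Protocol article*

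**What the plan says.** The relevant statements in the protocol article are spread over several sections.

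- **Concealment mechanism {16b}** consists of one statement: "Access to the computer-generated randomization scheme will be limited to the site coordinator and only be accessed at the time of allocation".
- **Implementation {16c}** gives the procedure. After consent, "the coordinator will access the computer-generated randomization file to discover which treatment arm the participant has been randomized to". The participant and the referring provider are then told the result.
- **Sequence generation {16a}** says that "A computer-generated randomization scheme has been generated for each site". It specifies 1:1 randomisation by site, stratified by comorbidity (yes/no) and psychotropic medication (yes/no), in permuted blocks of three.
- **Recruitment {15}**: "each site will be supported by a research coordinator who will be responsible for consenting eligible participants".
- **Who will take informed consent? {26a}**: "At their first contact with the coordinator, the coordinator will review details about the study aims, procedures, and risks following a script". For those still interested, "oral consent will be obtained to conduct a brief screening interview to confirm eligibility". After that, "participants who express the desire to participate in the study will then review the consent form with the coordinator".
- **Eligibility criteria {10}** leaves the judgement on eligibility to the referring sleep medicine provider.
- **Trial design {8}** places consent and baseline questionnaires before randomisation.
- **Who will be blinded {17a}** says that participants and clinicians cannot be blinded. The biostatistician receives masked data.

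**The concern.** Concealment has to work against the people who decide whether and when a patient enters. Here the only role with access to the list is the role that recruits. Restricting access to the coordinator keeps the list from everyone except the person best placed to act on it. Opening it only at allocation is a rule of conduct, not a barrier.

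A coordinator who has seen, or can work out, the next assignment in a stratum could be influenced by it, even without intent. The timing of a consent, the confirmation of eligibility or the yes/no classification of comorbidity could each be affected. The Discussion gives a plausible motive, since it holds that patients with severe insomnia and complex comorbidity need in-person care. If harder-to-treat patients tended to go to ICAU, the digital hub would look better and non-inferiority would be easier to declare. The main outcomes are self-reported by unblinded participants, so outcome assessment offers no protection either.

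**Working it through.** The article gives no figure for concealment, so there is none to reproduce. The check traces roles and then asks what could be known in advance.

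**Step 1: who does what.**

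- First contact and explanation of the study: coordinator ({26a}).
- Eligibility decision: referring provider ({10}).
- Screening interview that confirms eligibility: described within the coordinator's contact, in the passive voice, with no other interviewer named ({26a}).
- Consent: coordinator ({15}, {26a}).
- Custody of the list: site coordinator only ({16b}).
- Revealing the assignment: coordinator, by opening the file ({16c}).

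Consent and list custody therefore rest with the same role. On the natural reading, so does confirmation of eligibility.

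**Step 2: what the timing rule protects.** Each site has one pre-generated scheme covering 2 × 2 = 4 strata. If the file is a readable list, the first permitted opening can show later rows, and full compliance with the rule does not prevent this. If later rows are locked or only one record is returned, the rule works better. The article describes no locking, no release of single assignments and no independent custodian.

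**Step 3: what could be deduced with the list hidden.** Assume an observer who knows the earlier assignments in the stratum and where each block starts. The share known with certainty is the average, over positions in the block, of the probability that the earlier assignments fix that position. A block of three cannot be split 1:1, so two constructions are considered.

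- *Blocks mixing 2:1 and 1:2 at random* (six equally likely sequences). Positions 1 and 2 are never certain. Position 3 is certain only when the first two assignments match, which is 2 of 6 sequences. The share is (0 + 0 + 1/3)/3 = 0.11. The best guess is right in (1/2 + 2/3 + 2/3)/3 = 0.61.
- *Every block at the same 2:1 split* (three equally likely sequences). Position 1 is never certain. Position 2 is certain in 1 of 3, when the single minority assignment came first. Position 3 is always certain. The share is (0 + 1/3 + 1)/3 = 0.44. The best guess is right in (2/3 + 2/3 + 1)/3 = 0.78.

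For comparison, a fixed block of four at 1:1 gives (0 + 0 + 1/3 + 1)/4 = 0.33. Correcting the block size alone would not settle concealment.

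**Step 4: scale against the margin.** The margin is d = 0.5. Suppose selection left a difference in expected outcome between arms, after ANCOVA adjustment, of b outcome SDs. It would move d by b and use b/0.5 of the margin. The document gives no value for b. As assumptions only, b = 0.05, 0.1 and 0.2 would use 10%, 20% and 40%.

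**The case against.** The strongest reply is that the article never says later assignments are displayed. Opening a file to find one participant's arm also fits a lookup that returns a single record, and file format is a detail that an article may leave to the full protocol. This stands. A reader might infer that upcoming assignments are visible and that allocation is not concealed, but the text does not support it. What remains is that a section devoted to the concealment mechanism names the recruiter as list holder and offers only a timing rule. That is a stated mechanism, not an omitted detail.

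Second, a reader might infer that the list holder decides who is eligible. The eligibility section gives that decision to the referring provider, who has no access to the list, and the coordinator works from a script at first contact. This narrows the concern to consent timing, confirmation of eligibility and stratum classification.

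Third, much of the right order is already in place: consent and baseline questionnaires come before randomisation, and the file is opened only after consent. This limits what can be done to the participant being allocated. It does not prevent knowledge of later rows from affecting the next one.

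Fourth, the ANCOVA adjusts for baseline ISI and other covariates, so it would be too strong to say that selection could not be corrected. Adjustment can deal with measured imbalance but not with unmeasured prognosis.

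Finally, 44% is the upper end and assumes a constant 2:1 split, which fits poorly with the stated 1:1 ratio. The mixed construction gives 11%. The conflict between a block of three and 1:1 allocation is a separate matter and adds no weight here.

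**Conclusion.** The point holds as a weakness in a stated mechanism: concealment from the recruiter is not ensured. It rests on the coordinator's double role, which the text states directly for consent and list custody and by natural reading for confirmation of eligibility. It does not depend on any of the percentages.

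The block structure puts the share of deducible assignments at 11% to 44%, conditional on how the block of three was built and on the observer knowing earlier assignments in the stratum and the block boundaries. If the file shows later rows, the share could reach 100%, but that is a condition and not something the article reports. Nor does the document show that selection has taken place or how large its effect would be. The shares of the margin in the working are illustrations on assumed values.

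The change is worth making because the trial is open-label with self-reported outcomes, and because steering complex patients to in-person care would favour a non-inferiority conclusion.

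**What to change.** Remove the coordinators' access to the list. Give it to someone not involved in enrolment, treatment or the masked analysis, or to a central system if one is available. Release one assignment at a time, only after eligibility, consent, strata and baseline questionnaires are recorded and locked. Rewrite the sections on concealment mechanism {16b} and implementation {16c} to match. If later rows are already hidden from the coordinator, say so there and state how.

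If enrolment has begun, apply the change to the remaining participants and report how earlier ones were allocated.

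The cost is a short amendment plus naming a custodian or setting up a release function. The article mentions electronic data capture but does not say that it can randomise, so a system solution should not be taken for granted. The company that supplies the platform under test also manages the data, so if its system is used, the protocol should state who can see the list. The small downside is that allocation then depends on the custodian or system being available.
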